**Figure 1 F1:**
[figure not shown]
EGeSOR flow chart.

### Study population

Inclusion criteria are age ≥70 years; macroscopic diagnosis of head and neck cancer [oral, oropharyngeal, hypopharyngeal, or laryngeal] awaiting histological confirmation; coverage by the French statutory health insurance system; and written informed consent obtained from the patient. Non-inclusion criteria are as follows: correctional facility inmate; legal guardianship; psychological, familial, social, or geographic conditions that might interfere with the conduct of the study; personal history of head and neck cancer; and rare tumour site [sinonasal or salivary gland]. To prevent selection bias limiting the general applicability of our findings, we are including consecutive patients who meet the eligibility criteria.

### Study intervention

The study intervention has four components.

(a) CGA before cancer treatment initiation, performed by a geriatrician [designated the ‘intervention geriatrician’ hereafter];

(b) participation of the intervention geriatrician in developing the cancer-treatment plan;

(c) standardised multidimensional geriatric therapeutic programme designed by the intervention geriatrician; and

(d) geriatric follow-up during cancer treatment and for 24 months after randomisation.

#### (a) CGA

The CGA is performed by the intervention geriatrician, after randomisation and before the multidisciplinary meeting during which the cancer-treatment plan is established. The CGA consists in a detailed medical, psychological, and social assessment including a careful medical history and physical examination. In accordance with SIOG recommendations for elderly cancer patients, seven domains are assessed routinely: functional status, mobility and fall risk, nutritional status
[25], cognitive status, mood, co-morbidities and medications, and social environment. These domains are assessed using validated tests, questionnaires, scores, and/or scales [Table 
1]. Pain is also evaluated using a verbal numeric scale. The CGA is performed by a senior geriatrician, in some cases with help from a trained healthcare worker [usually a nurse working in the oncology and/or geriatric department].

**Table 1 T1:** Primary and secondary endpoints in the EGeSOR trial

**Endpoints**	**Time assessed**	**Description**
Primary endpoint	6 months after randomisation	Composite criterion including
		- death,
		- at least 2-point decrease in the Activities of Daily Living (ADL) score versus baseline
		- at least 10% decrease in body weight versus baseline
Secondary endpoints	6, 12, and 24 months after randomisation	- each component of the primary endpoint
		- progression-free survival
		- in-hospital death
		- unplanned admissions
		- post-surgery hospital stay length
		- discharge to home or nursing home
		- final cancer treatment plan (surgery, chemotherapy, targeted therapies, radiotherapy, and/or supportive care, alone or combined)
		- quality of life assessed by EORTC QLQ-C30 and specific module for head and neck cancer H&N35
		- treatment toxicities and/or complications: chemotherapy toxicities according to Classification Common Terminology Criteria for Adverse Events (CTCAE version 4.02)
		- cancer treatment feasibility
		- costs

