**Methods/design:**

EGeSOR is an open-label, multicentre, randomised, controlled, parallel-group trial in patients aged 70 years or older and receiving standard care for HNSCC. The intervention includes four components: the CGA conducted by a geriatrician before cancer treatment, participation of the same geriatrician in cancer treatment selection, a standardised geriatric therapeutic intervention designed by the same geriatrician; and geriatric follow-up for 24 months. The primary endpoint, assessed after 6 months, is a composite criterion including death, functional impairment [Activities of Daily Living score decrease ≥2], and weight loss ≥10%. Secondary endpoints include progression-free survival, unscheduled admissions, quality of life, treatment toxicities, costs, and completion of the planned cancer treatment. A centralised online system is used to perform 1:1 randomisation with a minimisation algorithm for centre, age, T and N stages, and tumour site [oral, oropharyngeal, hypopharyngeal, or laryngeal]. The estimated sample size is 704 patients, who are being recruited by 14 centres in 9 French cities.

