#### (b) Geriatrician participation in development of the cancer-treatment plan

The intervention geriatrician lists all identified problems by order of priority and provides specific advice on the treatment goal [curative or palliative] and modalities [surgery, radiotherapy, chemotherapy, targeted therapy, and supportive care, used sequentially or simultaneously] in a written report given to the ENT physicians in charge of cancer treatment. The intervention geriatrician then participates in the multidisciplinary meeting held to determine the cancer-treatment plan
[23].

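### Post-surgery stay is compared in a subset that the intervention can help to select, and treatment completion is judged against a plan that it helps to set

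*Protocol article*

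**What the plan says.** The CGA takes place "after randomisation and before the multidisciplinary meeting during which the cancer-treatment plan is established" (section (a) CGA). One of the four intervention components is "participation of the intervention geriatrician in developing the cancer-treatment plan" (Study intervention). Section (b) adds that the geriatrician "provides specific advice on the treatment goal [curative or palliative] and modalities" and then attends the meeting that settles the plan.

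Four secondary endpoints in Table 1 bear on this:

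- "post-surgery hospital stay length";
- "treatment toxicities and/or complications: chemotherapy toxicities according to Classification Common Terminology Criteria for Adverse Events";
- cancer treatment feasibility, which appears in the abstract as "completion of the planned cancer treatment";
- "final cancer treatment plan (surgery, chemotherapy, targeted therapies, radiotherapy, and/or supportive care, alone or combined", so the plan is itself an outcome.

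The Statistical analysis section states intention-to-treat for the primary endpoint and applies the primary-endpoint method to the secondary endpoints. It gives no population for the endpoints above and does not say how patients without surgery or chemotherapy count. The Discussion expects better feasibility and shorter hospital stay, and also expects the CGA to improve treatment selection. Its limitations paragraph does not mention that some endpoints depend on the plan.

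**The concern.** Randomisation makes the arms comparable when all randomised patients are compared. It does not do so for a subset formed later by a decision that the allocated arm can influence. Operated patients are such a subset. If geriatric input changes which patients go to surgery, operated patients differ between arms in frailty, and length of stay differs with them, even if no patient recovers faster. The planned adjustment for imbalanced baseline characteristics does not restore the lost comparability.

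Completion has a different weakness. Even with every randomised patient counted, each patient is judged against an individual plan, and in one arm the intervention helped to write that plan. A lighter plan is likely to be easier to complete. A higher completion rate could then reflect better support, less treatment, or both. This matters here because the Background itself names suboptimal treatment, chosen out of concern about toxicity, as a possible cause of poor survival in older patients.

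**Working it through.** **Order of events.** Randomisation; then CGA (intervention arm); then the multidisciplinary meeting with the geriatrician present (intervention arm); then the plan; then surgery or not; then a post-surgery stay or none. The variable that defines the subset lies downstream of allocation.

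**What each endpoint needs.**

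- Post-surgery stay needs an operation. No choice of analysis set can supply a value for an unoperated patient.
- Toxicity or complication can be scored yes or no in everyone randomised.
- Completion can also be scored in everyone randomised, but the yardstick may differ by arm.

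**Illustration.** The plan states no figure on this point. The only input taken from it is 704/2 = 352 patients per arm. Everything else is assumed:

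- 40% of patients are frail, and all controls are treated intensively, including surgery;
- mean stay is 12 days (fit) and 20 days (frail);
- completion is 85% (fit) and 55% (frail) on the intensive plan, and 85% (frail) on a lighter plan without surgery;
- toxicity is 30% (fit) and 55% (frail) on the intensive plan, and 15% (frail) on the lighter plan;
- within a given plan nobody benefits from the intervention.

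Let s be the share of frail intervention patients moved to the lighter plan.

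- Mean stay among operated patients = [0.6×12 + 0.4(1−s)×20] / [0.6 + 0.4(1−s)]
- Completion of own plan = 0.6×0.85 + 0.4[(1−s)×0.55 + s×0.85]
- Intensive plan completed, per randomised patient = 0.6×0.85 + 0.4(1−s)×0.55
- Toxicity, all randomised = 0.6×0.30 + 0.4[(1−s)×0.55 + s×0.15]

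| s (share of arm moved) | Mean stay, operated (days) | Own plan completed | Intensive plan completed | Toxicity, all randomised |
|---|---|---|---|---|
| 0 (controls) | 15.2 | 73.0% | 73.0% | 40.0% |
| 0.10 (4%) | 15.0 | 74.2% | 70.8% | 38.4% |
| 0.25 (10%) | 14.7 | 76.0% | 67.5% | 36.0% |
| 0.50 (20%) | 14.0 | 79.0% | 62.0% | 32.0% |

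Example for s = 0.25: stay = (7.2 + 6.0)/0.9 = 14.7 days; completion = 0.51 + 0.4×0.625 = 76.0%.

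**Chance of a significant result in favour of the intervention** (352 per arm, two-sided 5%, so 2.5% in this direction if s = 0). At s = 0.50, toxicity: z = 0.08/√(2×0.36×0.64/352) = 2.21, chance = Φ(2.21 − 1.96), about 60%. Completion: z = 0.06/√(2×0.76×0.24/352) = 1.86, chance about 46%. At s = 0.25 the chances are about 19% and 15%; at s = 0.10, about 6% and 5%.

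**Opposite shift.** Suppose controls are the ones treated more lightly, with s = 0.25, and the intervention arm is treated intensively throughout. Mean stay among operated patients is then 14.7 days in controls and 15.2 in the intervention arm. The same selection now counts against the intervention.

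**The case against.** A reader might infer that none of the three comparisons is randomised and that all of them tilt towards the intervention. The documents do not support that.

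- **Population.** No section restricts toxicity or completion to treated patients. Table 1 covers toxicities and complications of treatment generally; CTCAE is named for the chemotherapy part. Counted in all randomised patients, both endpoints compare randomised groups under two strategies, and shaping the plan is part of the strategy tested. A condensed article may also leave denominators to the full protocol or SAP.
- **Direction.** The Background's worry about undertreatment makes more intensive plans a possible result of the CGA. The tilt would then reverse.
- **Safeguards.** The final plan is reported by arm, so a shift would be visible. Death and progression-free survival could show harm from undertreatment, and unplanned admissions do not depend on surgery.
- **Claims.** The Discussion ties expected feasibility to follow-up that includes adjusting treatments. It does not promise a pure gain in tolerance.
- **Size.** Every rate above is assumed, and a small shift has little effect.

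All of this stands, and it limits the point on toxicity and completion to denominator and interpretation. It does not rescue post-surgery stay, because the condition on surgery is built into the endpoint and a later choice of denominator cannot remove it. Seeing the final plan by arm would reveal a shift but not correct the comparison.

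**Conclusion.** The point holds fully for post-surgery stay: its between-arm comparison rests on a subset chosen after randomisation, with a planned influence on that choice in one arm only, and can be biased in either direction. For completion it holds as a limit on interpretation: a difference cannot by itself be read as better tolerance. For toxicity, the comparison is valid as a whole-strategy effect provided all randomised patients are counted.

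The size of any bias cannot be computed, because the documents give no rates of plan change, surgery, toxicity or completion. In the illustration the stay difference runs from 0.2 to 1.2 days as the share of the arm moved rises from 4% to 20%, and is zero without a shift. The conclusion on post-surgery stay needs only that the geriatrician's advice can change who is operated on, which the intervention is designed to allow. The primary endpoint and the sample size are untouched.

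**What to change.** 1. For the between-arm comparison, replace post-surgery stay with total hospital days, or days alive and out of hospital, to 6 months in all randomised patients. The second option avoids counting early death as a short stay. Keep post-surgery stay as a descriptive result among operated patients.
2. State that toxicity or complications and treatment completion are analysed with all randomised patients as denominator and interpreted as effects of the whole strategy.
3. Report both beside the final treatment plan by arm, so that readers can see whether a difference comes with a change in treatment.

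The cost is mainly wording. The Costs section already provides for prospective recording of resources by the same method in both groups, including acute admissions for any reason. The team should confirm that planned surgical stays are captured with dates as well. The downside is that total hospital days are less specific to surgical recovery.

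Two further ideas are debatable, and I would not require them. Recording provisional treatment intent before allocation cannot be done validly for patients already enrolled, and histology is still awaited at inclusion. Counting completed curative-intent treatment per randomised patient would penalise whichever arm sets more palliative goals.

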#### (b) Geriatrician participation in development of the cancer-treatment plan

The intervention geriatrician lists all identified problems by order of priority and provides specific advice on the treatment goal [curative or palliative] and modalities [surgery, radiotherapy, chemotherapy, targeted therapy, and supportive care, used sequentially or simultaneously] in a written report given to the ENT physicians in charge of cancer treatment. The intervention geriatrician then participates in the multidisciplinary meeting held to determine the cancer-treatment plan
[23].

#### (c) A standardised multidimensional geriatric therapeutic programme

A geriatric therapeutic programme is implemented at baseline and during follow-up. The intervention geriatrician designs this programme based on the CGA findings, in cooperation with the ENT physicians, other ENT healthcare staff, and outpatient healthcare professionals. The programme has four components: optimising the management of problems detected in the seven health domains evaluated during the CGA, a medication review, patient education on co-morbidity self-management, and information on cancer treatments
[26]. These components are standardised and compliant with the most recent recommendations issued by the French National Authority for Health [HAS], French Society for Gerontology and Geriatrics, and French Society for Cardiology, as appropriate [Table 
2]. Regarding co-morbidities, the geriatric intervention focuses on the five most common conditions present in elderly patients with head and neck cancer: chronic atrial fibrillation, chronic heart failure, diabetes, coronary artery disease, and hypertension. Corrective measures are taken as required. A geriatrician specialised in geriatric oncology [name] is available by phone or e-mail for discussion with the intervention geriatrician. Careful attention is directed to complaints of pain. Analgesic medications are adjusted as needed and patients referred to a pain clinic if appropriate.

**Table 2 T2:** Standardised multidimensional geriatric therapeutic programme in the intervention arm of the EGeSOR trial; ADL, Activities of Daily Living score; IADL, Instrumental Activities of Daily Living score; MNA, Mini-Nutritional Assessment; BMI, body mass index; MMSE, Mini-Mental State Examination; GDS, Geriatric Depression Scale; CIRS-G, Cumulative Illness Rating Scale-Geriatrics

**Domains**	**Assessment tools – thresholds for interventions**	**Standardised responses**
Functional status	ADL ≤5	Social services notification
	AND/OR	Home care
	IADL ≤ 7	Access to geriatric network
Mobility/fall risk	Falls during the last 6 months	Walking and/or standing-balance rehabilitation (20 sessions)
	AND/OR	AND
	One-leg standing test <5 seconds	Fall management^(1)^
	AND/OR	
	Timed get-up-and-go test >20 seconds	
Nutritional status	MNA ≤ 17	Nutritional care according to severity of malnutrition and swallowing disorders^(2)^
	AND/OR	- Dietician visits
	Weight loss ≥5% in the last 3 months	- High-energy and high-protein diet
	AND/OR	- Nutritional supplements
	Weight loss ≥10% in the last 6 months	- Enteral nutrition
	AND/OR	- Monitoring of local/regional treatment prescribed by the ENT physician, including oral care^(3)^
	BMI < 21 Kg/m^2^	- Access to geriatric network
		- Education on disease self-management
Cognitive status	MMSE ≤ 23	- Evaluation for causes of delirium and correction of predisposing factors^(4)^
		- Neuropsychological assessment with evaluation of memory
		- Access to geriatric network
Depression	GDS-15 ≥ 6	- Antidepressant treatment^(5)^
		- Follow-up by a psychologist
		- Psychiatrist visit, depending on severity
		- Access to geriatric network
Co-morbidities	CIRS-G:	- Medication review and medication regimen optimisation^(6)^
	at least one co-morbidity (other than the HNSCC) grade ≥3	- Access to geriatric network
	AND/OR	- Education on disease self-management:
	Number of drugs ≥5/day	- Diabetes in the elderly: facts and management^(7)^ - Atrial fibrillation: facts and management^(8)^
	Focus on five diseases: chronic atrial fibrillation, chronic systolic heart disease, diabetes, coronary artery disease, hypertension	- Management of coronary heart disease in older adults^(9)^
		- Diagnosis and management of chronic systolic heart disease

^(1)^Assessment and prevention of falls in older people – Practice guidelines. Online in April 2009.

^(2)^Malnutrition in the elderly - Nutritional support strategy. Practice guidelines. Online in June 2007.

Physiotherapy - Preserving motor function in frail elderly people living at home Practice guidelines. Online in April 2005.

^(3)^Upper aerodigestive cancers - Practice guidelines ALD n°30. Online in November 2009.

^(4)^Alzheimer's disease and related conditions - Diagnosis and treatment: Practice guidelines. Online in December 2011.

^(5)^A workshop on psychotropic drug prescriptions in the elderly. Online in October 2007.

^(6)^Improving the primary care prescription of hypnotic and anxiolytic drugs in the French elderly. Online in March 2009.

^(6)^Improving drug prescription in older persons. Online in November 2012.

^(7)^Guidelines for the management and care of diabetes in the elderly. Online in January 2011.

^(8)^Guidelines for the management of patients with atrial fibrillation. Online in July 2007.

All guidelines available at
http://www.has-sante.fr/portail/jcms/fc_1249588/fr/accueil-2012/ Last accessed 27 December 2013.

Expert consensus of the French Society for Geriatrics and Gerontology and French Society for Cardiology on the management of atrial fibrillation in elderly people (2013), at
http://www.sfcardio.fr/.

^(9)^ Consensus of the French Society for Gerontology and Geriatrics and French Society for Cardiology for the management of coronary heart disease, at
http://www.sfcardio.fr.

^(10)^ Therapeutic education in patients with chronic heart failure : proposal for multiprofessional structured programme by a French task force under the auspices of the French Society of Cardiology at
http://www.sfcardio.fr.

#### (d) Geriatric follow-up

The standardised geriatric follow-up provided by the intervention geriatrician, consists in a brief assessment of nutrition, mood, pain, functional status, the five above-listed co-morbidities, self-perceived health status, medication use, and implementation of the multidimensional geriatric therapeutic programme. The results of this standardised follow-up are used to make recommendations to the ENT physician, oncologist, radiotherapist and general practitioner.Follow-up includes closely spaced physical examinations for 1 to 6 months depending on the treatment modalities; Figure 
2 is an example for a surgically managed patient. After completion of the initial cancer treatment, the intervention geriatrician or nurse phones the patient every 3 months during the first 2 years after randomisation. If problems are identified during any of these phone calls, an appointment for a visit with the intervention geriatrician is scheduled.

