## Methods/design

### Study design and setting

We are conducting an open-label, multicentre, parallel-group, randomised, controlled trial in patients aged 70 years or older and receiving standard care for HNSCC. One group receives a CGA-based multi-component intervention and the other does not [Figure 
1]. The primary endpoint is a composite criterion to be assessed after 6 months. Other endpoints such as OS and disease-free survival are assessed after 24 months. The patients are being recruited at 14 ENT/maxillo-facial surgery departments in 13 hospitals located in 9 cities in France [Paris, Créteil, Montfermeil, Villeneuve-Saint-Georges, Lille, Strasbourg, Nancy, Nantes, and Suresnes]. The protocol was approved by the appropriate ethics committee [CPP Ile-de-France I, Paris, France, approval April, the 20 April 2013;13213]. The trial is registered on ClinicalTrials.gov [NCT02025062].

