### Endpoints

Table 
2 shows the primary and secondary endpoints. The primary endpoint is a composite criterion evaluated 6 months after randomisation and including death, an at least 2-point decrease in the Activities of Daily Living [ADL] score
[27] versus baseline, and at least 10% weight loss versus baseline. A clinical research assistant blinded to the randomisation arm uses a standardised measurement guide to adjudicate the ADL score and weight. Weight is measured to the nearest 0.1 Kg using an electronic scale [Seca Model 876, Birmingham, United Kingdom]. Our decision to include functional and nutritional measures into the primary endpoint rests both on sound evidence that these measures influence treatment feasibility, patient survival, and quality of life; and on the potential for appropriate management to reverse functional impairments and weight loss.

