### Costs

We will estimate the cost of our four-component intervention, compare the costs of the intervention and control management strategies, and compute an incremental cost-effectiveness ratio. Costs will be estimated from the perspective of the French healthcare system, from randomisation to death or end of follow-up. Only direct costs will be counted. In each patient, all resources used will be recorded prospectively, using the same methodology in both groups. Resources used include the CGA [physician visits, medical interventions, and investigations], treatments [surgery, cytotoxic or targeted chemotherapy, radiotherapy, and supportive treatments (including recombinant human erythropoietin, anti-emetics, and colony-stimulating factors)], nutritional care [nutritional supplements and enteral nutrition], acute admissions for any reason, residence in a nursing home or rehabilitation unit, community care [physician visits and investigations during follow- up, number of physiotherapist sessions, number of home healthcare professional visits, and care provided at skilled nursing facilities]. The cost per resource unit will be taken from the cost lists established by the French statutory healthcare system. Differences in costs and differences in effectiveness on the primary endpoint will be used to estimate the incremental cost-effectiveness ratio. Costs will be reported as median [25th-75^th^ percentiles] and mean [SD] and compared using the Wilcoxon-Mann–Whitney test and parametric tests. Confidence intervals will be estimated by bootstrapping with 1000 re-samplings of the original dataset.

The significance level will be 5%. All tests will be two-tailed. Data will be analysed using Stata Software [College Station, TX, USA].

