The EGeSOR trial has several limitations. First, the CGA is time consuming and requires extensive involvement of geriatric teams, which may not be available in some centres. We visited each of the study centres to verify that the number of geriatricians was sufficient, and we considered reinforcing the geriatric team if necessary. Second, the primary endpoint is a composite criterion. However, demonstrating superiority of the study intervention on a single endpoint would have required such a large sample size as to compromise feasibility of the trial. Third, contamination bias may occur between the intervention and control groups, as each ENT physician manages patients in both groups. Conceivably, ENT physicians may apply knowledge acquired by managing intervention patients to their control patients, for instance by asking geriatricians for advice regarding vulnerable controls. Such contamination bias would diminish the size of the effect of the intervention. However, any contamination bias is probably limited, since modifications potentially introduced by ENT physicians in controls would have a very small effect compared to the full four-component intervention. Nevertheless, we are recording the number of times that advice from geriatricians is provided for control patients. Our study had several strengths. To our knowledge, it is the first randomised controlled trial evaluating the efficacy of the CGA in elderly cancer patients. We decreased the risk of selection bias by using randomisation with minimisation, the risk of evaluation bias by selecting objective clinical endpoints and using independent adjudication, and the risk of confusion bias by using randomisation with minimisation and a pre-specified multivariate analysis to correct for any baseline between-group imbalances. Finally, the standardised multidimensional geriatric therapeutic programme was designed in accordance with the most recent clinical recommendations and relied on validated international measurement tools.

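### Toxicities and complications are compared between arms that differ by design in contact, with no blinded grading stated; for admissions, only the unblinded unplanned label remains open

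*Protocol article*

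**What the plan says.** The protocol article, under Study design and setting, describes the trial as open-label ("We are conducting an open-label, multicentre, parallel-group, randomised, controlled trial in patients aged 70 years or older") and separates the arms by the intervention: "One group receives a CGA-based multi-component intervention and the other does not".

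The fourth component of that intervention is set out under (d) Geriatric follow-up. It starts with examinations: "Follow-up includes closely spaced physical examinations for 1 to 6 months depending on the treatment modalities". Once initial cancer treatment is complete, "the intervention geriatrician or nurse phones the patient every 3 months during the first 2 years after randomisation". A problem found on a call leads to a booked geriatric visit. Results become recommendations to the ENT physician, oncologist, radiotherapist and general practitioner.

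Table 1 lists unplanned admissions and "treatment toxicities and/or complications: chemotherapy toxicities according to Classification Common Terminology Criteria" among the secondary endpoints, at 6, 12 and 24 months, with no difference by arm. Under Statistical analysis, secondary endpoints are compared in the same way as the primary one: chi-square test, relative risk and absolute difference.

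On blinding, the Endpoints section says: "A clinical research assistant blinded to the randomisation arm uses a standardised measurement guide to adjudicate the ADL score and weight". The Discussion says the trial reduced "the risk of evaluation bias by selecting objective clinical endpoints and using independent adjudication". For costs, "all resources used will be recorded prospectively, using the same methodology in both groups", and the resources listed include acute admissions of every cause.

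**The concern.** How many toxicities are recorded depends partly on how often someone looks and asks. Here the number of contacts differs between arms because contact is part of what is being tested. The geriatric assessments cover nutrition, pain, mood and function, where the effects of head and neck cancer treatment can show, and what they find is passed to the treating team. Low-grade or short-lived events could then be noticed and written down more often in the intervention arm. Whoever grades them may know the arm, since masking is described only for ADL and weight.

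Unequal detection would raise recorded toxicity in the intervention arm, which could create apparent harm or hide a benefit. Unblinded grading could act in either direction.

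For admissions the issue is narrower. Whether an admission counts as unplanned is a judgement. The intervention adds booked visits and access to a day hospital and rehabilitation unit, so a similar episode might be labelled differently in the two arms. The Discussion expects fewer unplanned admissions, so the label matters to a result the authors hope to report.

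**Working it through.** The plan gives no toxicity rate, admission rate or detection probability, so it has no figure of its own on this point to reproduce. The check is first a comparison of the text, then an illustration on stated assumptions.

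**Step 1: the text, endpoint by endpoint.**

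| | ADL and weight | Toxicities and complications | Unplanned admissions |
|---|---|---|---|
| Common assessment times | Yes | Yes (6, 12, 24 months) | Yes (6, 12, 24 months) |
| Same recording method in both arms stated | Standardised measurement guide | Not stated | Yes for acute admissions of any cause, under Costs |
| Scale or definition named | ADL score; weight by scale | CTCAE 4.02, chemotherapy only | None given for the label |
| Blinded adjudication stated | Yes | No | No |

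Toxicities and complications have the least stated protection. For admissions, occurrence is covered by the Costs section and only the label is open.

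**Step 2: contact by schedule.** Assume initial treatment ends by month 6. In months 6 to 24 the common assessments are at 12 and 24 (2), and the calls would fall at 9, 12, 15, 18, 21 and 24 (6). This shows that the planned schedules differ. It does not measure recorded toxicity, because routine cancer visits and hospital records also capture events in both arms.

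**Step 3: what unequal recording would do.** Let the true rate p be equal in both arms, with n = 320 per arm (the Sample size estimation figure before the loss allowance). Let s1 = 90% be the share of affected patients recorded in the intervention arm and s0 the share in controls. The observed rates are a = p·s1 and b = p·s0, so the apparent relative risk is s1/s0. With d = |a − b|, pooled standard error se0 and unpooled se1,

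P(significant) = Φ((d − 1.96·se0)/se1) + Φ((−d − 1.96·se0)/se1).

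Worked case, p = 30% and s0 = 80%: a = 0.27, b = 0.24, d = 0.03, and the mean rate is 0.255. Then se0 = √(0.255 × 0.745 × 2/320) = 0.0345 and se1 = √((0.27 × 0.73 + 0.24 × 0.76)/320) = 0.0344. The result is 0.138 + 0.002 = 14%.

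| True rate in both arms | s0 = 85% (RR 1.06) | s0 = 80% (RR 1.13) | s0 = 70% (RR 1.29) |
|---|---|---|---|
| 20% | 6% | 10% | 28% |
| 30% | 7% | 14% | 43% |
| 50% | 10% | 25% | 73% |

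With s0 = 90% the relative risk is 1.00 and the rate is the nominal 5%.

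**Step 4: masking a benefit.** Take true rates of 20% against 30% (relative risk 0.67). Recording of 90% against 80% shows 0.18/0.24 = 0.75; 90% against 70% shows 0.18/0.21 = 0.86.

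All recording shares and toxicity rates in Steps 3 and 4 are assumptions.

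**The case against.** The strongest reply is that the article never says geriatric visits or calls feed the toxicity data. The listed content of the follow-up includes neither toxicity grading nor admissions, and the endpoint times are common to both arms. Who records and grades toxicity, and the control arm's routine visits, may be set out in the full protocol or the figures, which are not shown. This stands, and it limits the point to a risk. It does not remove the point, because the article itself fixes unequal contact, sends the findings to the treating clinicians and names masking for two measures only.

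A reader might infer that the harm comparison is biased, with toxicity against the intervention and unplanned admissions in its favour. The documents do not support that. Acute admissions are recorded by one method in both arms. An admission truly averted by a call or booked visit is an effect of the intervention, not an artefact.

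A reader might also turn the 2 against 6 contacts into a size of bias. An event lasting 1, 2 or 3 months with uniform onset over those 18 months is current at a common assessment in 2/18, 4/18 or 6/18 of cases (11%, 22%, 33%), and at a call in 6/18, 12/18 or 18/18 (33%, 67%, 100%). The arithmetic is right, but it ignores routine cancer visits and records and leaves out the initial treatment period.

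Finally, the Discussion's remark on evaluation bias can be read as meaning the primary endpoint only. That reading is fair, but the sentence sets no such limit.

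**Conclusion.** The point holds as a risk. Toxicities and complications are open to unequal detection and unblinded classification, chiefly for low-grade events and for surgical or radiotherapy events outside the named chemotherapy scale. For admissions, only the unblinded unplanned label remains.

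The size of either bias cannot be derived from the documents. The illustration shows that, if recording differed by 10 percentage points (90% against 80%), the false-positive rate would be 10% to 25% over true rates of 20% to 50%, against the nominal 5%. If recording were equal, there would be no excess. These are secondary endpoints; the primary endpoint and its sample size are not affected.

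**What to change.** 1. Make toxicities and complications of grade 3 or higher, or leading to admission, the main between-arm comparison, taken from the same sources and at the same time points in both arms. Say how events outside the chemotherapy scale are graded. Flag events known only from geriatric visits or calls, and repeat the comparison without them as a sensitivity analysis. Deleting those events outright would be weaker, because geriatric findings also reach the common records; for the same reason the sensitivity analysis is only a partial check. Masked grading alone would not correct unequal detection.
2. From the resource-use data already planned, report by arm the patients with at least one acute admission for any reason, beside the unplanned subset. A fall in the subset without a fall in the total would point to labelling.
3. Limit the evaluation-bias statement in the Discussion to the endpoints that are adjudicated.

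The cost is one source field on the toxicity form, slightly more analysis and some rewording, with no extra visits or patients. The downside is that low-grade events carry less weight in the main toxicity comparison.
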